# 2. Study Hypotheses and Objectives

The purpose of this study is to develop a safe and effective challenge model to LPS in terms of induction of ICAM-1, and so provide a robust framework for the clinical assessment of future anti-inflammatory therapies directed specifically against ICAM-1.

- 1. **Hypothesis**

The nasal ICAM-1, cellular and cytokine/chemokine responses will be reproducible and show a dose response in relation to the amount of LPS used to challenge.

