## Regimen Assignment

Subjects will be assigned to a sequence in accordance with the randomisation schedule generated prior to the start of the study. The randomisation will be balanced over the 5 nasal challenge sequences and will be generated using RandAll, the GSK web-server based clinical trials randomisation validated system.

A description of each challenge sequence is provided in Table 1. The LPS dose corresponds to the dose administered to each nostril.

Table 1. Nasal LPS Dosage Regimen Sequence

| Sequence | Number of subjects receiving sequence | Nasal Challenge 1 | Nasal Challenge 2 | Nasal Challenge 3 | Nasal Challenge 4 | Nasal Challenge 5 |
| --- | --- | --- | --- | --- | --- | --- |
| 1 | 3 | placebo | 1μg LPS | 10μg LPS | 30μg LPS | 100μg LPS |
| 2 | 3 | 1μg LPS | 30μg LPS | placebo | 100μg LPS | 10μg LPS |
| 3 | 3 | 10μg LPS | 100μg LPS | 30μg LPS | 1μg LPS | placebo |
| 4 | 3 | 30μg LPS | 10μg LPS | 100μg LPS | placebo | 1μg LPS |
| 5 | 3 | 100μg LPS | Placebo | 1μg LPS | 10μg LPS | 30μg LPS |

A washout time of 12-28 days will be employed between challenges

1. **Samples and Measures**

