### 8.3.2 Statistical Analyses

Each of the measures will be summarised descriptively by dose and time using appropriate summary statistics. If appropriate, response variables will be transformed (e.g. log-transformed). Gene expression data will be normalised by house-keeper gene. The TNSS will be calculated by summing the scores of nasal blockage, nasal discharge/rhinorrhoea, nasal burning/itching/pain sensation, and sneezing at each timepoint. Weighted means of symptom scores will be calculated over the time interval 0 to 10h.

TNSS, nasal sniff pressures, nasosorption measures and gene expression data from the nasal scrapes will each be plotted against time, with a separate plot for each subject and measure, and with LPS dose and placebo represented by separate lines on the plots. Summary statistics (e.g. mean +/- 95% confidence intervals or median and interquartile range) for nasal lavage and gene expression data will be plotted by dose against time.

Correlations will be explored using scatter plots for the following measures:

- Weighted means TNSS vs. maximum TNF-α
- Weighted means TNSS vs. maximum IL-8
- Weighted means TNSS vs. maximum s-ICAM-1
- Maximum ICAM-1 expression vs. maximum TNF-α

Reproducibility of the nasal LPS challenge for ICAM-1 expression and TNF-α will be explored using the following subsets of data:

- Predose data for each period to explore intra-subject variability.
  Parameter vs. period number will be plotted with a separate line for each subject to explore whether there is a period effect. Box and whisker plots will also be used to summarise the parameter by period.
- Placebo period data – Parameter vs time will be plotted with a separate line for each subject to explore whether there is a time-course effect. Box and whisker plots will also be used to summarise the parameter over time.

Box and whisker plots for ICAM-1 expression and TNF-α and dose and time will be presented to investigate whether these measures return to baseline after 24h.

Additional exploratory analyses may be performed to further characterize the expression profile of ICAM following nasal LPS challenge.

1. **Study Schedule**

|  | Screening | Sessions 1-5 | | | | | | | | | | | | | | Tel F/up |
| --- | --- | --- | --- | --- | --- | --- | --- | --- | --- | --- | --- | --- | --- | --- | --- | --- |
|  |  | -30m to  -15m | 0 | 30m | 1h | 2h | 3h | 4h | 5h | 6h | 7h | 8h | 9h | 10h | 24h |  |

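### The planned reproducibility checks contain no value taken after LPS, so they cannot show whether the ICAM-1 or TNF-α response drifts over a subject's four LPS challenges

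*Protocol*

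**What the plan says.** Section 8.3.2 introduces the reproducibility work with "Reproducibility of the nasal LPS challenge for ICAM-1 expression and TNF-α will be explored using the following subsets of data" and then names two subsets.

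- The first is "Predose data for each period to explore intra-subject variability", displayed as follows: "Parameter vs. period number will be plotted with a separate line for each subject to explore whether there is a period effect". Box plots by period are added.
- The second is "Placebo period data – Parameter vs time will be plotted with a separate line for each subject to explore whether there is a time-course effect", with box plots over time.

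The main post-challenge output is not by period: "Each of the measures will be summarised descriptively by dose and time using appropriate summary statistics". The remaining displays are individual or summary profiles over time by dose, box plots by dose and time, and scatter plots of session summaries. The section closes with an open clause: "Additional exploratory analyses may be performed to further characterize the expression profile of ICAM following nasal LPS challenge".

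The hypothesis in section 2 is that the nasal responses to LPS are reproducible and dose-related. Section 2.2 makes reproducible induction of ICAM-1 part of the primary question. Section 2 gives the purpose of the model: to "provide a robust framework for the clinical assessment of future anti-inflammatory therapies". Under Regimen Assignment, Table 1 gives each subject four LPS doses and one placebo in five periods, and "A washout time of 12-28 days will be employed between challenges".

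**The concern.** Induction is a post-dose quantity. Pre-dose values can show a lasting shift in baseline or a residue of the previous challenge. They cannot show tolerance or priming that appears only when LPS is given again. The placebo subset shows how the measures behave over a session without LPS, which is useful but is not the response either. A flat pre-dose plot would therefore be consistent with a response that falls or rises from one LPS challenge to the next, and the listed outputs would not separate the two cases.

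At stake is how far the trial can support a claim that the response is reproducible. No subject receives the same dose twice, so there is no same-dose repeat to fall back on. Comparing responses across periods, adjusted for dose, is the only internal evidence on repeated challenge.

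**Working it through.** The protocol states no figure to reproduce: section 8.2.1 bases the sample size on feasibility and gives no SD, effect size or power. Results are in units of σ, the within-subject SD of the per-session response. The 5% two-sided level and 80% power are assumptions.

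**Inputs from Table 1.** Five sequences with 3 subjects each. Every treatment occurs once in each period, so with 15 completers period is balanced against dose and subject. Each subject has 4 LPS sessions, 60 in all.

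**Precision of a drift estimated from the LPS sessions** (subject + dose + linear period):

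- For a subject whose placebo falls d periods from the middle period, the within-subject sum of squares of period over the 4 LPS sessions is 10 − d² − d²/4 = 10 − 1.25d².
- Across the five sequences d² is 4, 0, 4, 1 and 1, total 10. The sum is 50 − 12.5 = 37.5 per set of five sequences, and 3 × 37.5 = 112.5 for 15 subjects.
- Dose takes nothing from this: each dose's periods sum to 15 over the five sequences, and so do the subject means of the LPS periods, (75 − 15)/4 = 15.
- SE = σ/√112.5 = 0.094σ per period. Giving placebo its own slope in the full 75-session model yields the same value.
- Error df = 60 − 15 − 3 − 1 = 41. Detectable slope = 0.0943 × (2.020 + 0.850) = 0.27σ per period.
- With number of prior LPS exposures in place of period, the SE is 0.116σ per exposure, detectable 0.116 × 2.87 = 0.33σ.
- With 12 completers, in the loss patterns tried, the SE per period is 0.103σ to 0.112σ.

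**Why the LPS sessions and not one common slope.** With all 75 sessions and one slope, the SE is σ/√150 = 0.082σ. If only the LPS response drifts, 12 of the 15 sessions in each period carry the drift, so the common slope recovers 12/15 = 80% of it.

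**Effect of adding period on the dose contrasts.**

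- 15 completers: the SE of each LPS-minus-placebo contrast stays at √(2/15) = 0.365σ; error df fall from 56 to 52.
- 12 completers: it goes from 0.408σ to 0.411σ (+0.7%) when losses are spread over sequences, and to 0.422σ (+3.3%) when one whole sequence is lost.

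**Carry-over.** Of the 20 possible ordered pairs of different treatments, 14 occur in Table 1 and six never do; placebo followed by 1 μg occurs in three sequences. With first-order carry-over terms, the SE of the 100 μg contrast rises from 0.365σ to 0.442σ. Drift separates cleanly from dose but less cleanly from carry-over.

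**Illustrations of size (assumed drifts).**

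- A 10% loss per LPS exposure leaves 0.9³ = 73% at the fourth challenge.
- If LPS sessions alone drift by b per period and this is ignored, the variance of a paired LPS-minus-placebo difference is multiplied by 1 + b² × 2.14/2, where 2.14 = 30/14 is the variance of a dose's period number over 15 subjects. For b = 0.1, 0.25 and 0.5σ the factors are 1.01, 1.07 and 1.27, so intervals widen by about 0.5%, 3% and 13%.

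**The case against.** The strongest reply is that this is a small exploratory study. Section 8.1 calls it hypothesis generating, section 8.3.2 plans descriptive summaries and plots, and no paired contrast or test is specified. The choice of a period term normally belongs in the SAP, which is not at hand. Post-dose data are collected in every session, individual profiles are plotted, and the open clause would permit a look by period.

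Much of this stands, and it lowers the stakes. It does not supply the check. The protocol does not leave the reproducibility data open: it names two subsets, and neither contains the response. The open clause is optional and names no analysis by period. An exploratory study can report an estimate with an interval without testing anything.

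Stronger readings are tempting but not supported:

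- A reader might infer that drift would bias the dose-response. Each dose occurs equally often in every period, so with a complete square a period drift common to all sessions cancels from the dose means.
- A reader might infer that ignored drift makes the dose contrasts much noisier. For drift confined to LPS sessions, that needs a large assumed value: 0.5σ per period is 2σ from first to last period and still widens intervals by only about 13%.
- A reader might infer five LPS exposures per subject. Table 1 gives four, and period number is not exposure number.
- A reader might infer harm to later drug studies. The protocol does not say that those would challenge the same person more than once.

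**Conclusion.** The point holds in a limited form. The outputs specified in section 8.3.2 cannot show whether the ICAM-1 or TNF-α response to LPS wanes or rises over a subject's four LPS challenges, although reproducibility of that response is part of the hypothesis and the primary question. Table 1 allows a linear drift to be estimated with an SE of about 0.094σ per period, detectable at about 0.27σ per period, given 15 completers, a linear pattern, negligible carry-over, a two-sided 5% level and 80% power. σ is not given in the protocol, so no size in measured units can be stated, and nothing in the protocol suggests that drift is present.

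It does not follow that drift must go unnoticed, since the data will exist, or that the dose-response is unsound. Nor would a drift estimate replace a same-dose repeat, which the design does not contain. Severity is optional to minor.

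**What to change.** Add to section 8.3.2, for ICAM-1 expression and TNF-α:

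- A per-session post-dose response, for example the log of a post-dose summary relative to the same session's pre-dose value. Session maxima of both measures are already needed for the planned scatter plots.
- A plot of this response by period and by LPS exposure number, one line per subject, with dose marked.
- A drift estimate with a 95% confidence interval and no formal test, from the LPS sessions: subject + dose + linear period, or number of prior LPS exposures in place of period. Equivalently, use all sessions and let placebo have its own slope.
- A sentence stating that the pre-dose plot checks baseline and carry-over only.

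The cost is a few lines of text, one small model per measure and a few error df, with no new samples. If period is also added to the dose model and only 12 complete, precision on dose contrasts falls by up to about 3% in the patterns tried. The report should state that drift cannot be fully separated from carry-over, because Table 1 is not balanced for it.

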**7.1 Samples**

- Nasosorption (right nostril) will be performed before and then 30min, 1h, 2h and hourly to 10h, 24h
- Nasal lavage (left nostril) will be performed at times before (-30 min, 2, 4, 8, 24h.
- Nasal scrape (left nostril) will be carried out after lavage on 4 occasions

……………before (-30 min), 3h, 6h, 24h.

The scrapes will be performed progressively more deeply into the posterior aspect of the nostril, from the inferior aspect of the inferior turbinate

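### The only display assigned to return to baseline at 24h is an unpaired group box plot; a by-dose summary of each subject's 24h-to-predose ratio is missing

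*Protocol*

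**What the plan says.** Section 8.3.2 (Statistical Analyses) names the question and the tool together: "Box and whisker plots for ICAM-1 expression and TNF-α and dose and time will be presented to investigate whether these measures return to baseline", the time in question being 24h. It names no change, ratio or difference from the same-session predose value, and no way of telling from the plot whether a measure has returned.

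Other statements bear on the point:

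- The general approach is descriptive: "Each of the measures will be summarised descriptively by dose and time using appropriate summary statistics".
- The plotted scale is left open: "If appropriate, response variables will be transformed (e.g. log-transformed"), and "Gene expression data will be normalised by house-keeper gene".
- TNSS, sniff pressures, nasosorption measures and scrape gene expression are plotted against time "with a separate plot for each subject and measure, and with LPS dose and placebo represented by separate lines on the plots".
- Predose values have a stated use across periods: "Predose data for each period to explore intra-subject variability", together with a look for a period effect.
- Placebo-period values are plotted over time, one line per subject, to look for a time-course effect.

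The samples for a paired comparison are already scheduled. Section 7.1 states "Nasosorption (right nostril) will be performed before and then 30min, 1h, 2h and hourly to 10h, 24h", and scrapes are taken "before (-30 min), 3h, 6h, 24h". The Study Schedule repeats this for all five sessions.

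**The concern.** Return to baseline asks whether a subject's 24h value has come back to that subject's own value before the challenge. A box plot by dose and time answers a different question: whether the distribution across subjects at 24h resembles the distribution at predose. If subjects differ widely in their usual ICAM-1 or TNF-α level, the boxes can overlap heavily while most subjects are still raised. With 12 to 15 subjects, lack of resolution can then be read as resolution.

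The sampling itself could also move the 24h value, since lavage, scraping and nasosorption are repeated through the day. The placebo session has the same sampling and is the natural reference. The plan looks at placebo over time but names no summary of the LPS change beside the placebo change.

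At stake is part of the time-course answer, which section 2.2 lists among the principal research questions for mediators and mRNA.

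**Working it through.** **Inputs from the protocol.** 15 recruited so that 12 complete (section 8.2.1); predose and 24h values in every session (section 7.1). Sample size rests on feasibility, so there is no power, SD or effect size to reproduce.

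**Assumptions, not in the protocol.** Equal SD at predose and 24h; within-session correlation ρ from 0.3 to 0.9; the residual shifts and log-scale SDs given below.

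**Step 1: what pairing is worth.** In SD units, the standard error (SE) of the 24h-minus-predose mean difference is √(2/n) if pairing is ignored and √(2(1−ρ)/n) if it is used. The ratio is 1/√(1−ρ), whatever n is.

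| ρ | Paired SE, n = 12 | Paired SE, n = 15 | Unpaired/paired |
|---|---|---|---|
| 0.3 | 0.342 | 0.306 | 1.20 |
| 0.5 | 0.289 | 0.258 | 1.41 |
| 0.7 | 0.224 | 0.200 | 1.83 |
| 0.8 | 0.183 | 0.163 | 2.24 |
| 0.9 | 0.129 | 0.115 | 3.16 |

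The unpaired SE is 0.408 for n = 12 and 0.365 for n = 15.

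**Step 2: how often a box plot would hide a shift.** 20,000 trials per setting were simulated from a bivariate normal with n = 12. The protocol gives no reading rule, so one plausible reading was used: is the 24h median inside the predose interquartile box? The paired reading was whether the 95% t-interval for the change excludes zero.

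| ρ | No shift: median in box | 0.5 SD shift: median in box | 0.5 SD shift: paired interval excludes 0 |
|---|---|---|---|
| 0.3 | 82% | 58% | 27% |
| 0.5 | 87% | 59% | 35% |
| 0.7 | 92% | 60% | 53% |
| 0.8 | 95% | 60% | 71% |
| 0.9 | 98% | 61% | 94% |

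With a persisting shift of 0.5 SD, about 6 trials in 10 still put the 24h median inside the box, and a higher correlation does not help that reading. For a shift of 0.8 SD the share in the box is 32% falling to 23%, and the paired interval excludes zero in 57% rising to 100%.

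**Step 3: an example on the log scale.** Take a response still 50% above baseline at 24h, d = ln 1.5 = 0.405, with n = 15, between-subject SD sb and within-subject SD sw.

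- Unpaired SE = √(2(sb² + sw²)/15)
- Paired SE = sw√(2/15)
- SE of the LPS change minus the placebo change = 2sw/√15
- Implied ρ = sb²/(sb² + sw²)

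| sb | sw | ρ | d/unpaired SE | d/paired SE | d/SE of change minus placebo change |
|---|---|---|---|---|---|
| 0.8 | 0.3 | 0.88 | 0.405/0.312 = 1.3 | 0.405/0.110 = 3.7 | 0.405/0.155 = 2.6 |
| 0.5 | 0.3 | 0.74 | 0.405/0.213 = 1.9 | 3.7 | 2.6 |
| 0.5 | 0.6 | 0.41 | 0.405/0.285 = 1.42 | 0.405/0.219 = 1.85 | 0.405/0.310 = 1.31 |

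With 12 completers each figure is multiplied by √(12/15) = 0.894; the first row becomes 1.2, 3.3 and 2.3.

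Subtracting the placebo change costs a factor of √2 in SE. In the last row it does worse than the unpaired reading. A plain within-subject LPS-minus-placebo difference at 24h has SE sw√(2/n), the same as the paired change, provided session-to-session shifts are negligible.

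**Step 4: what the interval would look like.** With n = 12 the t quantile on 11 df is 2.201. For sw = 0.3 the half-width is 2.201 × 0.3 × √(2/12) = 0.270, a factor of 1.31, so a ratio of 1.5 has limits 1.15 and 1.96. For sw = 0.6 the half-width is 0.539, a factor of 1.71, giving 0.87 and 2.57. The second is plainly inconclusive, and the reader can see that it is.

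**The case against.** The strongest reply is that the pairing is already on view. The per-subject time plots show each subject's predose and 24h values, with a line per dose and one for placebo, for s-ICAM-1, TNF-α and scrape gene expression. The placebo-period and predose-by-period plots cover part of the reference and session questions. The study is declared hypothesis generating (section 8.1), further exploratory ICAM analyses are left open, and derived change variables are commonly defined in a SAP, which is not shown.

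Most of this stands, and it rules out several stronger inferences:

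- That the plan discards the predose value: the per-subject plots keep it.
- That the box plots show raw levels: the scale is not fixed. Log transformation is allowed and house-keeper normalisation required, though neither is a baseline correction.
- That a decision rule is built on the box plots: the text only says they serve to investigate.
- That a predose covariate would cut residual variance by 1 − r², or 25% to 49% at r = 0.5 to 0.7: subject effects already drop out of within-subject dose comparisons in a crossover, so that reduction does not carry over. The protocol also specifies no estimation model.
- That the 24h result sets the spacing of sessions in later trials: the protocol makes no such link.

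What the reply does not meet is narrower. Up to 15 separate plots per measure show the pairing but do not summarise it by dose. The one display the protocol assigns to the question is the one that breaks the pairing. Being exploratory excuses the absence of a test, but not a summary that does not match its question.

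**Conclusion.** The point holds in a limited form. The display tied to return to baseline is unpaired, and no by-dose summary of the paired change is named, although the data are collected. A modest persisting response can therefore be missed.

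The size depends on assumptions. The SE is 1.2 to 3.2 times larger without pairing for ρ of 0.3 to 0.9, and the gain is small at the low end. The favourable example of 3.7 against 1.3 to 1.9 SE rests on a within-subject SD of 0.3 and 15 subjects; at 0.6 with a between-subject SD of 0.5 the comparison is 1.85 against 1.42. Even then an interval helps, because it shows the answer to be uncertain where overlapping boxes invite the reading that the response has gone.

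This is a cheap improvement to a descriptive analysis. It does not show that the plan states anything false.

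**What to change.** In section 8.3.2, extend the return-to-baseline sentence as follows:

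1. For each subject and session, derive log(24h/predose) for ICAM-1 expression and TNF-α, using that session's predose sample.
2. Summarise it for each LPS dose and for placebo as a geometric mean ratio with 95% CI.
3. Show the within-subject LPS-versus-placebo comparison at 24h alongside, with its interval.
4. Keep the box plots, drawn on the ratio.
5. Describe a wide interval as inconclusive, not as a return to baseline.

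No equivalence margin is required, since the protocol gives none and the study is not confirmatory. No predose covariate is required either.

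The cost is a few derived variables and some wording; no samples or visits are added. With 12 to 15 subjects, some 24h results will have to be reported as inconclusive.
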